## Control group

Each infant in the control group will receive no training. All participants in the trial will receive health education. This includes group counseling focusing on daily activity and diet. The participants will be asked not to participate in any other rehabilitation treatments.

## Outcome measures

The baseline and follow-up evaluations will be performed by experienced pediatric assessors blinded to the group assignments when the patient is at 1, 4, 6, 12 and 24 months CA.

### Primary outcome measure

Motor development will be measured using the Peabody Developmental Motor Scales-II (PDMS-II) via the motor quotient. Motor development is measured at 1, 4, 6, 12 and 24 months CA with the PDMS-II by an assessor blinded to the group assignments. The use of the PDMS-II is recommended [40] and has been widely used as a motor development outcome measure for patients with CHD [41–46]. Both fine and gross motor function can be assessed by the PDMS-II. The PDMS-II is valid for children aged from term to 76 months. The PDMS-2 contains six subtests, including reflexes, stationary, locomotion, object manipulation, grasping and visual-motor integration. The results of the subtests may be used to generate a Gross Motor Quotient, a Fine Motor Quotient and a Total Motor Quotient, which are three global indices of motor development. A previous study demonstrated that the PDMS-II had high test-retest reliability and acceptable responsiveness to intervention effects [47].

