### Methods/Design

A prospective and randomized controlled trial involving passive movement and active exercise in very young CHD infants with cardiac catheterization will be performed. The aim of the study is to determine:whether passive movement and active exercise beginning at 1 month of corrected age (CA) in infants with CHD improves motor development at 24 months of CA compared with control subjects,the potential benefits of exercise on growth, heart function and bone quality of very young infants with CHD, andthe potential adverse effects related to passive movement and active exercise.

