## Study design

The CHD patients with cardiac catheterization will be recruited from and investigated at the Xin Hua Hospital affiliated to the Shanghai Jiao Tong University School of Medicine, Shanghai City, China.

Prior to inclusion, the following information will be obtained for all patients: demographic data (for example, gestational age at birth, birth weight, CA, and gender), medical history (for example, the duration of intensive care unit and hospital stay, and age of cardiac catheterization), heart defect (for example, defect type and size), and type of feeding (for example, breast or artificial feeding). Each patient’s parents will be asked to sign an informed consent form before the patient can participate in the study.

Eligible participants will be randomized by a 1:1:1 allocation ratio by computer either to the exercise intervention group, in which they will receive passive movement and active exercise to promote motor development; the home-based intervention group, in which they will receive passive movement and active exercise from parents or caregivers at home; or the control group, in which they receive follow up only (Fig. 1). The total study duration will be 23 months, which consists of a 3-month intervention and 20-month follow-up period without intervention. All patients will receive the exercise intervention, the home-based intervention, or the control conditions as allocated. All patients will be assessed at 1, 4, 6, 12 and 24 months CA.

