## Statistical analysis

The SPSS 20.0 and Microsoft Excel 2013 software will be used for statistical analyses. Demographic data will be described with descriptive statistics, including the mean ± standard deviation (SD). We will use analysis of covariance to compare the primary and secondary outcomes of the three groups. A general linear model will be used to compute mean outcome values adjusted for diagnosis, gender and socioeconomic status (SES), with the group as the fixed factor and diagnosis, gender and SES as covariates. If patients are lost to follow-up, an intention-to-treat analysis will be performed. Statistical significance is set at a p-value less than 0.05.

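### The primary motor quotient is not named, the 24-month visit in the aim is not carried into the sample size or analysis, and the planned three-group test does not by itself answer the versus-control question

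*Protocol article*

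**What the plan says.** All references are to the protocol article.

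- **Aim (Methods/Design).** The first aim asks whether the exercise programme "improves motor development at 24 months of CA compared with control subjects". It gives a visit and a comparator but names no quotient.
- **Primary outcome measure.** "Motor development will be measured using the Peabody Developmental Motor Scales-II (PDMS-II) via the motor quotient", in the singular. The same section then says that the subtests may yield "a Gross Motor Quotient, a Fine Motor Quotient and a Total Motor Quotient, which are three global indices of motor development", and nothing marks one of them as primary. It adds "Motor development is measured at 1, 4, 6, 12 and 24 months CA with the PDMS-II", with no age singled out.
- **Sample size calculation.** The motor quotient is again singular. The target is a 0.5 SD difference among the three groups, with 42 infants per group for 80% power at two-sided 0.05, raised to 49 for attrition. No visit is given.
- **Statistical analysis.** "We will use analysis of covariance to compare the primary and secondary outcomes of the three groups". The model has group as the fixed factor and diagnosis, gender and socioeconomic status as covariates. It has no term for visit and no contrast with control. "Statistical significance is set at a p-value less than 0.05".

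**The concern.** A primary endpoint needs one variable, one time and one comparison. Here the variable is open among three, the time appears only in the aim, and the comparison in the analysis differs from the one in the aim.

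Two consequences follow. First, whoever runs the analysis can choose the quotient after seeing the data, and the nominal 5% then no longer describes the error rate of the claim. Second, a significant three-group test says only that the three means are not all equal. It does not say which arm differs from control, or in which direction. The trial could report a positive primary result and still not have answered whether exercise improves motor development over control.

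**Working it through.** **Inputs from the article.** Three groups at 1:1:1; 42 analysed per group (126 in total); alpha 0.05; 0.5 SD; three quotients; four post-baseline visits (4, 6, 12 and 24 months CA). **Assumed, because the article gives no values:** gross-fine correlation 0.3 to 0.7, between-visit correlation 0.3 to 0.7, and Total taken as the sum of Gross and Fine. Covariates are left out.

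**1. The plan's own figure.** The 42 per group does not follow from the stated inputs. A one-way three-group F test at 80% power needs 53 per group for f = 0.25, 59 for f = 0.2357 (one mean 0.5 SD from two equal means) and 79 for f = 0.2041 (means evenly spaced over 0.5 SD). This is a separate matter. Here 42 is used only as the planned number analysed.

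**2. False-positive risk from the open quotient.**
- One quotient, one visit, one three-group test: 0.05.
- Three quotients at 24 months, if independent: 1 − 0.95³ = 0.143. This is only an upper benchmark, since Total is built from the other two. Simulated under the null with correlated quotients: about 0.08 to 0.11.
- Three quotients at four visits, if all twelve counted as primary and were independent: 1 − 0.95¹² = 0.46. Simulated with correlation: about 0.20 to 0.30 over most of the range, and up to 0.34 at the lowest correlations.

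**3. The three-group test against the aim.** An illustration with observed means, in SD units: control 0, exercise +0.30, home-based −0.30, 42 per group, residual SD 1.
- F = 42 × (0.30² + 0.30²) / 2 = 3.78 on 2 and 123 df. The critical value is 3.07 and p is about 0.026, so the result is significant.
- Each arm against control: t = 0.30 / √(2/42) = 0.30 / 0.218 = 1.37, p about 0.17.
- Exercise against home-based: t = 0.60 / 0.218 = 2.75, p about 0.007.

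The planned test is positive, yet neither comparison with control is. If the two exercise arms truly differ, at least one of them must differ from control. But the three-group test does not say which, and does not separate benefit from harm.

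**4. Contrasts with control, if added.** Two unadjusted contrasts on one quotient at 24 months give a familywise error of about 0.09 under the null (0.0975 if independent).

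Power for 0.5 SD is Φ(0.5 × √(n/2) − 1.96):
- n = 42: Φ(2.29 − 1.96) = 0.63.
- n = 49, if no infant is lost: Φ(2.47 − 1.96) = 0.70.
- n = 42 with each contrast at 0.025: Φ(2.29 − 2.24) = 0.52.
- n = 42 when the three-group test must be significant first: simulated at about 0.55 if the other exercise arm equals either control or the first arm. If that arm lies midway, the three-group test itself has 51% power, so the gated contrast cannot exceed that.

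**The case against.** A reader might infer that all three quotients at all four visits are to be tested as primary at 0.05, which would put the false-positive risk at several times nominal. The article does not support that. The motor quotient is singular wherever it is called primary, apart from the abstract's plural for outcome measures. The three quotients are introduced as indices that may be generated, in a description of the instrument. The five ages are the general visit schedule, repeated elsewhere for all assessments. The first aim names 24 months CA, and reading the analysis together with the aim is more natural than counting twelve primary tests. A count that also includes contrasts with control at every visit describes analyses the article does not plan.

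It is also fair to say that a three-group test followed by contrasts is ordinary practice, and that this is a condensed article. A multiplicity rule and the follow-up contrasts may be in an analysis plan that is not shown, so their absence is not counted here.

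What survives does not depend on that missing plan. The choice of primary quotient belongs to the definition of the endpoint. The comparison stated in the aim and the comparison stated in the sample size and analysis sections are not the same.

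**Conclusion.** The point holds in a limited form. The primary quotient is not fixed, the aim's 24-month visit is not carried into the sample size or analysis, and the three-group analysis of covariance does not by itself answer the versus-control question.

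On the reading most favourable to the plan, with the visit taken as 24 months, the open quotient raises the false-positive risk from 5% to about 8 to 11%, roughly double. The 20 to 30% range applies only on the twelve-test reading, which the article does not state. Both ranges rest on assumed correlations. The mismatch between aim and test rests on the text alone and needs no assumption. This is a cheap improvement to the plan and does not call for a redesign.

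**What to change.** - **Endpoint.** Name one quotient at 24 months CA as the single primary endpoint. The Total Motor Quotient is one option. The choice is the sponsor's, since the aim names none.
- **Test sequence.** Test the three-group effect at 0.05. Only if it is significant, test exercise against control and home-based against control, each at 0.05, with confidence intervals. With three groups this needs no split of alpha. If all three means are equal, the first test holds the error at 5%. If only one exercise arm equals control, there is a single true null contrast with control, and it is tested at 5%.
- **Everything else.** Make the other two quotients and the 4-, 6- and 12-month results secondary.
- **Timing.** Recruitment is under way, so fix this before any results by group are seen.

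**Cost.** No extra infants or visits are needed. Early-visit or single-domain results can no longer be claimed as primary. The power of each contrast should be stated openly: for 0.5 SD at 42 per group, about 63% for the contrast alone and about 55% when gated by the three-group test, before any gain from covariates. Splitting alpha instead, with each contrast at 0.025 and no gate, would give about 52%.

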### Secondary outcome measures

The Ross score will be evaluated using a modified Ross scoring system. The Ross scoring system [48] was first described by Ross [49] for infants. Then, Reithmann et al. [50] and Läer et al. [51] modified the system. The modified Ross scoring system is used in the clinical evaluation of patients with CHD. It consists of diaphoresis, tachypnea, breathing with abdominal retractions, respiratory rate, heart rate, and hepatomegaly. Each variable receives a score of 0, 1, or 2 points according to severity. The range of the total score is from 0 to 12 points with higher values indicating more severe impact. An experienced pediatric cardiologist grades the six variables.Ventricular function will be assessed using echocardiography, which is a useful noninvasive method. In patients with CHD, the measurement of ventricular function using echocardiography is a standard procedure [52]. The left ventricular function is an important variable. The most commonly utilized indices of the left ventricular function are the left ventricular ejection fraction and fractional shortening [48]. Echocardiographic assessment of the patients is performed by an experienced pediatric cardiologist. Echocardiographic assessment of crying children is performed approximately 5 minutes after they become calm.Bone quality will be measured using a quantitative ultrasound machine (Omnisense 7000P, Sunlight Medical Inc., Israel). Quantitative ultrasound measurements provide a safe, non-invasive method for obtaining information on bone quality. The quantitative ultrasound method is designed to measure the speed of sound (SOS) at a peripheral site (such as the distal 1/3 of the radius and middle of the tibia [53]) by axial transmission. The measurement site is defined as the distal 1/3 of the radius. The mean of three measurements of the radius SOS is used for analysis. The z-score is given in terms of the standard deviation from the average of population of same age and gender. The z-score is defined as the difference between the raw score to be standardized and the mean difference divided by the standard deviation (a z-score less than or equal to −2.0 indicates low bone quality and a z-score greater than −2 indicates normal bone quality). The z-score is predictive of bone quality in children [54, 55]. All quantitative ultrasound measurements are performed by the same trained pediatrician.Anthropometric measurements, including body length, weight, head circumference and upper arm circumference, will be measured. Body length is measured without shoes. Weight is measured with light clothing using digital scale (Seca Digital Column Scale and Seca 376 Baby Scale). Head circumference and upper arm circumference are measured with a nonflexible tape.Adverse events related to exercise will be recorded.

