**Methods/Design:**

A prospective and randomized controlled trial will be conducted in very young CHD infants with cardiac catheterization. A total of 147 infants with CHD will be randomized by a 1:1:1 allocation ratio by computer to an exercise intervention group, a home-based intervention group and a control group. The exercise intervention group will receive passive movement and active exercise from experienced physiotherapists in pediatrics three times a week for 12 weeks. The home-based intervention group will receive passive movement and active exercise from their parents or caregivers at home three times a week for 12 weeks. The control group will receive follow up only. The follow-up duration is 20 months. The primary outcome measures are the motor quotient measured by the Peabody Developmental Motor Scales-II. The secondary outcome measures are the Ross score, ventricular function, bone quality, body length, weight, head circumference, upper arm circumference, and adverse events.

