**Fig. 1 Fig1:**
[figure not shown]
Flowchart. CHD indicates congenital heart disease; *CA* corrected age, *PDMS-II* Peabody Developmental Motor Scales-II

If the pediatrician evaluating the patient prescribes additional physiotherapy, the patient will receive physiotherapy. The pediatrician will record information if the participant receives other physiotherapy.

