## Withdrawal management

The patients with CHD who have any of the following conditions will be allowed or will be asked to withdraw from the study:The patient’s parents require withdrawal.The patient develops heart failure, or respiratory failure, or other serious diseases.The exercises lead to any adverse effects.

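### The adverse-event outcome is defined by relatedness to exercise, so the planned three-group comparison sets attributed events against a control arm that can have almost none

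*Protocol article*

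**What the plan says.** The abstract of the protocol article (Methods/Design) lists the secondary outcomes, ending with "bone quality, body length, weight, head circumference, upper arm circumference, and adverse events". No limit by relatedness is given there. The section Secondary outcome measures, the only place where this outcome is made operational, says "Adverse events related to exercise will be recorded". The third study aim (Methods/Design) is likewise worded as adverse effects related to the movement and exercise programme.

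The section Control group says "Each infant in the control group will receive no training", and adds: "The participants will be asked not to participate in any other rehabilitation treatments". Study design leaves one exception open: "If the pediatrician evaluating the patient prescribes additional physiotherapy, the patient will receive physiotherapy".

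The section Statistical analysis covers every secondary outcome with one sentence: "We will use analysis of covariance to compare the primary and secondary outcomes of the three groups".

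**The concern.** Whether an intervention adds risk can be judged only against the background rate of events without it. Infants with heart disease can be expected to fall ill in every arm; the withdrawal section itself anticipates heart failure, respiratory failure and other serious illness. If an event enters the record only once it is judged related to exercise, the background rate in the control arm is never collected. No later analysis plan can recover it.

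The contrast could then mislead either way. Background illness that is called exercise-related appears as an excess over a near-empty control arm. Illness that is put down to the heart defect leaves no trace in the outcome, whether or not exercise contributed. In both cases the result depends on attribution.

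**Working it through.** There is no stated figure to reproduce: the point rests on how the outcome is defined. The passages are set side by side first, and an illustration follows.

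**1. Who can have a qualifying event?**

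| Arm | Study exercise | Possible source of an exercise-related event |
|---|---|---|
| Exercise intervention | Yes, by physiotherapists | Study exercise |
| Home-based intervention | Yes, by parents or caregivers | Study exercise |
| Control | None | Only physiotherapy prescribed by the pediatrician |

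The control count is therefore close to a structural zero, although not strictly zero.

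**2. Is observation equal?** No. Parents in the exercise arm keep a daily compliance record (Intervention group). Parents in the home arm record the infant's reaction daily and are telephoned weekly (Home-based intervention group). For controls the article describes only the scheduled assessments and health education. Simply widening the definition would leave this imbalance in place.

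**3. Does the planned method suit the data?** For a yes/no event the within-arm variance is p(1 − p). With 0 of 49 it is 0. With 6 of 49 it is 0.122 × 0.878 = 0.107. Analysis of covariance assumes a common residual variance, which fails when one arm has none.

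**4. Illustration under assumed counts.** Inputs: 49 per arm and two-sided 0.05 (Sample size calculation); control count fixed at 0. Fisher's exact test is used for the illustration and is not the planned test. With equal arms and all x events in one arm,

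p = 2 × C(49, x) / C(98, x).

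For x = 6: 2 × (49·48·47·46·45·44)/(98·97·96·95·94·93) = 2 × 0.0133 = 0.027.

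| Events called related, exercise v control | p |
|---|---|
| 4 v 0 | 0.117 |
| 5 v 0 | 0.056 |
| 6 v 0 | 0.027 |
| 7 v 0 | 0.012 |
| 10 v 0 | 0.001 |

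Now suppose the true all-cause rate is the same in both arms, so exercise does nothing, and a fraction of the exercise-arm events is called related. Expected count = 49 × rate × fraction, rounded.

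| Assumed rate, both arms | Fraction called related | Count v 0 | p |
|---|---|---|---|
| 10% | 0.5 | 2.45 → 2 | 0.495 |
| 20% | 0.5 | 4.9 → 5 | 0.056 |
| 30% | 0.2 | 2.94 → 3 | 0.242 |
| 30% | 0.5 | 7.35 → 7 | 0.012 |
| 50% | 0.5 | 12.25 → 12 | 0.0002 |

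The true risk difference is nil in every row. Only the rate and the attribution fraction move the p-value.

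**5. What an all-event comparison could show.** With n = 49 per arm, Δ the difference and p̄ the mean of the two rates,

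power = Φ{[Δ − 1.96√(2p̄(1 − p̄)/n)] / √[(p₁(1 − p₁) + p₂(1 − p₂))/n]}.

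For 10% v 30%: (0.2 − 1.96 × 0.0808)/0.0782 = 0.53, so power is about 70%. For 20% v 40% it is about 58%, and for 30% v 50% about 52%. These rates are assumptions too. The comparison would be interpretable but only moderately powered.

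**The case against.** The strongest reply is that the text is read too literally. It never says that only exercise-related events are recorded, the abstract's wording is unrestricted, and this is a condensed article whose full protocol may hold an all-event form. That is fair as far as it goes: a reader might infer that other events are deliberately excluded, and the documents do not say so. What stands is that the sole operational rule is the restricted one. The abstract's broader wording makes the article inconsistent and does not repair the rule.

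A reader might also infer that the control count is zero by definition. Prescribed physiotherapy is allowed in any arm, so a stray control event is conceivable.

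A third tempting inference is that the safety aim cannot be answered. The first aim names control subjects as comparator; the third names none. A descriptive account of events tied to exercise would meet it as written, and physiotherapist-delivered and parent-delivered exercise can still be compared. What fails is the comparison with control that the statistical section implies.

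Serious deterioration also has other routes into the data. Withdrawal for heart or respiratory failure applies in every arm, and the Ross score and echocardiography are outcomes in all three. These soften the problem for cardiac harm. They do not capture non-cardiac or non-serious events, and the remaining safety-related withdrawal condition, "The exercises lead to any adverse effects", again depends on exercise.

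Finally, no event rate is given, and the scenarios can point in opposite directions. Neither the direction nor the size of any bias is established. Nor does the article say who judges relatedness, so it cannot be shown that the judgement is unblinded, although blinding is stated only for the baseline and follow-up evaluations.

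**Conclusion.** The point holds as a flaw in the definition and planned comparison of one secondary outcome. If the article is followed as written, the three-group contrast for adverse events compares attributed events with a near-structural zero and reflects attribution, not excess risk. This rests on the sentence in Secondary outcome measures being the operative rule; if the full protocol already records all events in all arms, only the wording needs correcting.

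The Fisher figures (p = 0.056 at five events, 0.027 at six) illustrate assumed counts and are not a forecast. The documents do not support the stronger claims that the safety aim is unanswerable or that real harm will be hidden. The objection to analysis of covariance here is confined to adverse events. The primary outcome is unaffected, but the change should be made soon because uncollected control-arm events cannot be restored later.

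**What to change.** Change the sentence in Secondary outcome measures so that all adverse events, serious and non-serious, are recorded in all three arms with the same form and the same schedule. Include a contact in every arm that covers the 12-week intervention period: forms at the scheduled follow-up visits alone would leave ascertainment driven by the daily records and weekly calls in the exercise arms. Enter relatedness afterwards as a separate field, so that it does not decide whether an event is recorded.

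In Statistical analysis, exempt adverse events from the analysis of covariance. Compare the proportions of infants with any event and with any serious event by risk differences with exact confidence intervals. Exercise-related events can still be described, and compared between the two exercise arms.

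Cost: a revised form and modest extra recording, with no change to treatment or sample size. Trial status says recruitment is underway, so control-arm data will be incomplete for infants already enrolled. Report how many infants were followed under each recording rule.

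### Adverse-event recording is limited to events related to exercise, so the adverse-event outcome cannot show an excess over the untrained control group

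*Protocol article*

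**What the plan says.** The Secondary outcome measures section ends with the one statement on which harms are collected: "Adverse events related to exercise will be recorded". No other section provides for recording events regardless of cause.

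The abstract describes the same outcome more widely. Its list of secondary outcomes closes with "head circumference, upper arm circumference, and adverse events", unqualified. The Statistical analysis section states: "We will use analysis of covariance to compare the primary and secondary outcomes of the three groups". It makes no exception for adverse events.

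On exposure, the Control group section says: "Each infant in the control group will receive no training". The abstract agrees: "The control group will receive follow up only". The third listed aim of the trial concerns possible harm from the exercise programme.

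Withdrawal management gives two further routes by which harm could surface. One applies in any arm: "The patient develops heart failure, or respiratory failure, or other serious diseases". The other depends on exercise: "The exercises lead to any adverse effects".

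**The concern.** Randomization supports a comparison of harms when the same kind of event is counted in every arm without regard to cause. Here relatedness to exercise is a condition for being recorded at all. In the control arm there is no study exercise for an event to be related to. In the exercise arms an event enters the data only after a causal judgement, and that judgement is not randomized. Blinded outcome assessment does not remove the problem, because whoever decides relatedness must know that the infant exercised.

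The error can go either way. Illness that exercise makes more frequent, but that nobody links to a session, is left out of the count. Ordinary infant illness that is blamed on exercise is set against a control count that stays at or near zero. No later choice of test can restore control events that were not collected, and the Trial status section says recruitment is underway.

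**Working it through.** **Reading the sections together**

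| Element | Section | Consequence |
|---|---|---|
| Outcome is adverse events, unqualified | Abstract | Applies to all infants |
| Recorded events are those related to exercise | Secondary outcome measures | Needs exposure and attribution |
| Controls have no training | Control group | Essentially no qualifying events |
| Secondary outcomes compared in three groups | Statistical analysis | Control count near zero by rule, not by observation |
| Serious illness leads to withdrawal, any arm | Withdrawal management | Surfaces as withdrawal, not as a recorded adverse event |
| Ross score and echocardiography, all arms | Secondary outcome measures; Outcome measures | Some cardiac harm visible at 1, 4, 6, 12 and 24 months CA |

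What these routes leave uncounted is illness, arrhythmia, injury or hospital admission between visits that is not attributed to exercise and does not lead to withdrawal.

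**Illustration of size**

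The plan states no adverse-event rate, power or margin, so there is no figure to reproduce. The inputs from the document are 49 infants per arm (Sample size calculation) and a 0.05 threshold (Statistical analysis). The event rates, the attribution fractions and the use of Fisher's exact test are assumptions.

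*Step 1: how few events make a difference.* With x of 49 events in one exercise arm and 0 of 49 in control, the two-sided Fisher p is 2 × C(49, x) / C(98, x).
- x = 5: p = 0.056
- x = 6: p = 0.027

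*Step 2: a false excess when exercise is harmless.* Let b be the background event rate in every arm and q the fraction of exercise-arm events called exercise-related. Recorded events in one exercise arm are then Binomial(49, b × q), and control is 0. The chance of p < 0.05 is the probability of 6 or more recorded events.

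| b | q = 0.25 | q = 0.5 | q = 1 |
|---|---|---|---|
| 10% | 0.1% | 3.5% | 36.5% |
| 20% | 3.5% | 36.5% | 94.5% |
| 30% | 15.9% | 76.4% | 99.9% |

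For b = 20% and q = 0.5, the expected recorded count is 49 × 0.20 × 0.5 = 4.9 in the exercise arm against 0 in control, although both arms truly expect 49 × 0.20 = 9.8 events.

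*Step 3: what recording all events would offer.* By the normal approximation for two proportions with 49 per arm, power is about 28% for 10% against 20%, 70% for 10% against 30%, and 58% for 20% against 40%. Fisher's test would give somewhat less. The comparison would be modest in power but interpretable.

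**The case against.** The strongest reply is that the sentence does not say other events go unrecorded. The abstract's wording is wider, and a journal article condenses a fuller protocol that may hold the event definitions and reporting forms. That is a fair limit, since reading the rule as exclusive is an inference. But the article does not leave the matter open. It states a restrictive rule, and if wider collection was intended, that rule conflicts with the abstract and still needs correcting.

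A reader might infer more than the documents support:

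- *That harm in general would go unseen, or that the third aim cannot be answered.* The Ross score and echocardiography are planned in all arms, and heart failure, respiratory failure and other serious disease are withdrawal grounds whatever the cause. The aim is weakened, not defeated.
- *That the control count is zero by definition.* The Study design section lets a pediatrician prescribe extra physiotherapy, so a control infant could in theory have a qualifying event. This would not restore a valid comparison.
- *That unblinded physiotherapists or parents make the causal judgement.* The article does not say who does.
- *That a specific adverse-event test is planned.* There is only the general sentence on secondary outcomes. The third aim's wording would also fit descriptive reporting in the exercise arms.

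The figures are open to challenge too. They depend on assumed rates and on a test the plan does not name, and with little attribution the false excess is rare. They show a mechanism and do not predict this trial's result.

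**Conclusion.** The point holds for the adverse-event outcome. Followed as written, the rule yields essentially no control events and an exercise-arm count governed by attribution, so a difference between arms cannot be read as harm and its absence cannot be read as safety. This rests on the ordinary reading of the only collection rule given and needs none of the assumed rates. Under those rates, the chance of a spurious difference with harmless exercise runs from 0.1% to 99.9%, which means the result would reflect how events are attributed more than how often they occur.

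The primary outcome is unaffected, and part of the cardiac risk is measured independently of attribution. The change should be made because a stated aim depends on this outcome and control events not collected now cannot be reliably reconstructed.

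**What to change.** Change the sentence in Secondary outcome measures so that all adverse events are recorded in all three arms from randomization to 24 months CA, regardless of suspected cause. Use the same form and schedule in each arm, at least at the existing 4, 6, 12 and 24-month visits. Keep relatedness to exercise as an added item on the form.

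Compare the three groups on infants with any event and infants with any serious event. Report exercise-related events descriptively in the two exercise arms only.

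The cost is one changed sentence, a short form at visits already planned, and more events to log, most of them probably ordinary childhood illness. Collection at visits alone also relies on parental recall over gaps of up to 24 − 12 = 12 months. Some events will be missed, but the recall interval is the same in all arms if the form and schedule are the same.
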